### Patient recruitment and group assignment

The pharmacist will inform the potential candidates about the study, will ask for their authorization to participate, and their decision, whether they want to participate or not, will be registered. In the case of patients who agree to participate, the variables related to the objectives of the study will be assessed and when they meet the inclusion criteria and sign the informed consent form they will be randomized to one of the two groups (intervention or control group). Patients who do not meet any of the inclusion criteria will be informed about it, and the respective registration will be filed.

### Withdrawal or termination from study

According to the investigator’s judgment or when applicable, patients and their families should be informed of circumstances under which their participation may be terminated by the investigator without the subject’s consent. Patients and their families should also be informed of procedures for safe and orderly termination should they decide to withdraw from the study before it is completed. In addition, patients may leave the study at any time. Patient’s data concerning the reason for withdrawal before completing the treatment will be registered and archived for statistical evaluation. Specific reasons for withdrawal or termination from study are: (1) voluntary withdrawal from the patient; (2) intervention is harmful to the health of the patient; (3) patient’s death; (4) development of exclusion criteria during the study or other safety reasons; or (5) non-compliance of the protocol. The intention-to-treat principle will be kept at all times and all subjects will be analyzed according to their allocated treatment group.

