### Study population

The researchers will recruit 200 volunteer patients diagnosed with BD-I, based on the Diagnostic and Statistical Manual of Mental Disorders, 4th edition (DSM-IV). BD-I patients are more likely to have poor adherence, rapid cycling, suicide attempts, and current anxiety or alcohol use disorder. Psychiatrists will refer patients who might meet the inclusion criteria to the pharmaceutical care program; subsequently, the pharmacist will evaluate whether each patient meets all the inclusion criteria and none of the exclusion criteria, and then invite the patient to participate in the study.

The inclusion criteria will be the following:

• Male or female, between 18 and 65 years of age, and diagnosed with BD-I based on the Diagnostic and Statistical Manual of Mental Disorders, 4th edition (DSM-IV), who have been discharged from or referred by the outpatient service of the SJDC.

• Living in Medellín, Sabaneta, Envigado, Itagüí, Bello, Copacabana, Girardota, Barbosa, Guarne, Rionegro, Marinilla, La Ceja, El Carmen de Viboral, El Retiro, San Vicente, La Unión, and El Santuario (Antioquia, Colombia).

The exclusion criteria will be the following:

• Patients with their first manic episode, schizoaffective disorder, BD-II, cyclothymia, and other bipolar spectrum disorders, personality disorders that seem like BD, and sociopathic disorder.

• Patients with epilepsy, infected with the HIV, chronic decompensated disease (blood pressure values above 180/110 mmHg, total cholesterol above 300 mg/dL, low density cholesterol greater than 160 mm/dL, hemoglobin A1c greater than 9%, oxygen saturation lower than 90%).

• Patients unable to comply with the protocol requirements, including severe alcohol and drug use.

• Pregnancy or breastfeeding.

• Patients with intellectual disability, presence of any cognitive impairment impeding the comprehension and signature of the informed consent form, or illiteracy.

• Patients who refuse to sign the informed consent form (consent must be obtained before any study-related procedures are conducted).

• Patients in electroconvulsive therapy.

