### Biostatistical considerations

Data will be analyzed according to the intention-to-treat principle. All patients will be analyzing according to their allocated treatment group. Statistical analysis will be blinded and performed using SPSS version 13.0 (IBM SPSS, Armonk, NY, USA). Control and intervention groups will be compared in terms of the proportion of changes from baseline to 12 months following. Repeated-measures analysis will carry out. Clinical assessments will be made at baseline and every 3 months during the study period. Follow-up will be continuing to complete the year, even if a relapse or psychiatric hospitalization occurred. The main end points of interest are the number and duration relapse events per person-year of follow-up and number of admissions to the hospital due to BD. Data will be reported as means and standard deviations (SD) or as percentages. The Pearson chi-square test (between study groups) and the McNemar test (within-group changes from baseline to follow-up at 12 months) will be used to compare proportions. Comparisons for categorical variables will be conducted by using Chi-square tests (the Fisher exact test when appropriate) and for continuous variables by using the independent-sample t test (Mann-Whitney U test when appropriate). The Mann-Whitney test will be used to compare outcomes between groups. For quality-of-life questionnaire the Student’s t test will be used if sample distribution proves to be normal. Otherwise, the Wilcoxon rank-sum test will be used. The paired Student’s t-test (within-group changes from baseline to follow-up at 12 months) or the independent sample Student’s t-test (between study groups) will be used to compare means; odds ratios (ORs) and 95% confidence intervals (CIs) will be estimated as well. Mean number and duration of relapse events normalized to person-time, will be compared between groups using the Student’s t test. Multivariable analyses will be performed to explain the association of multiple variables associated with the factors significantly related to primary outcome: hospitalizations, readmission, relapse and total number of episodes of illness, number and total days of hospitalizations, days of illness, and days of free intervals per year. The sociodemographic and clinical variables to assess will be: duration previous episodes, severity of depression or mania, polarity of the last episode (manic, hypomanic, depressive, or mixed), co-morbid psychiatric illness, social support, psychosocial factors, educational level, living in rural area, having a history of violence to others, having no insight, non-compliance to medication, lack of practical support from the family. Analysis of depression and mania episodes, adherence to pharmacotherapy and quality of life will be performed, using repeated measure analysis. Comparisons will be analyzed using two-tailed tests, *P* <0.05 will be considered as statistically significant.

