
### Missing data

According to Little and Rubin [28], the missing-data mechanism will be performed through the multiple imputation method, to replace missing values and to calculate accurate estimates of standard errors. The procedures all rest on the assumption that data are missing at random (MAR). We will include all non-missing values or outcomes at all time points and baseline demographics in the models that generated imputed estimates (that is, the likelihood of missing a follow-up visit can be predicted by available baseline or past observed data [29]). In addition, the multiple imputation method combines the likelihood-based analysis from each completed dataset is approximately equivalent to the analysis based on the observed-data likelihood, whereas the imputation uncertainty is reflected by the variation across the multiple completed datasets [30]. According to the definition of Fisher *et al.*[31], the intent-to-treat analysis will be include all randomized patients in the groups to which they were randomly assigned, regardless of their adherence with the entry criteria, regardless of the treatment they actually received, and regardless of subsequent withdrawal from treatment or deviation from the protocol [32]. The variable follow-up time for individual subjects, both the number of relapse events and duration of relapses during the follow-up will be calculated as the number (or duration (weeks)) of events per person per year of follow-up.

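### Terminating patients from the study for protocol non-compliance or a newly met exclusion criterion conflicts with the plan's intention-to-treat definition and its aim of a full year of follow-up

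*Protocol article*

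**What the plan says.** The section Withdrawal or termination from study introduces its list with "Specific reasons for withdrawal or termination from study are". The list therefore ends participation in the study, not only receipt of the pharmacist's intervention. Reason (2) is harm from the intervention. The last two reasons are "4) development of exclusion criteria during the study or other safety reasons; or (5) non-compliance of the protocol". The section closes with "The intention-to-treat principle will be kept at all times and all subjects will be analyzed according to their allocated treatment group".

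The exclusion criteria in Study population, which reason (4) turns into exit criteria, include "Patients unable to comply with the protocol requirements, including severe alcohol and drug use", "Patients in electroconvulsive therapy" and the limits "total cholesterol above 300 mg/dL, low density cholesterol greater than 160 mm/dL".

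Three other places bear on the point:

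- Biostatistical considerations: "Follow-up will be continuing to complete the year, even if a relapse or psychiatric hospitalization occurred".
- Missing data: intention-to-treat covers all randomized patients whether or not they met the entry criteria, deviated from the protocol or withdrew from treatment. Missing values are multiply imputed under missing at random (MAR), using all observed outcomes and baseline demographics.
- Study completion and Data collection: on ethical grounds, all patients are followed by telephone and by review of the medical history at routine appointments.

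**The concern.** An intention-to-treat analysis needs outcomes on the patients it promises to include. Reason (5) removes from observation those who deviate from the protocol, whom the Missing data section says must be kept. Reason (4) removes those who come to meet an exclusion criterion after entry. If observation stops at termination, their hospitalizations, emergency consultations and unscheduled visits up to month 12 must be imputed although they could have been collected.

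The loss may not be neutral. Cholesterol and treatment adherence are secondary outcomes, and non-compliance to medication is a planned explanatory variable for the primary outcome. Electroconvulsive therapy and severe substance use may plausibly accompany a worse course, although the article does not say so.

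Detection may also depend on the arm. The intervention group has weekly calls and appointments, whereas control visits are three-monthly, although the Discussion mentions some calls to control patients. One unblinded pharmacist follows both groups and collects the data.

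**Working it through.** **1. The passages side by side**

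| Question | Withdrawal section | Elsewhere in the article |
|---|---|---|
| Does a protocol deviator stay in? | Reason (5): participation ends | Missing data: included in the analysis |
| Does a patient who meets an exclusion criterion later stay in? | Reason (4): participation ends | Missing data: included whatever the entry-criteria status (wording about eligibility at entry, so a near match) |
| Does stopping end observation? | Yes, the list is about leaving the study | Missing data speaks only of withdrawal from treatment. Biostatistical considerations aims to complete the year |
| Are outcomes collected after termination? | Not stated | Not stated. The calls and record review are given an ethical purpose and are not tied to outcome collection in terminated patients |

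**2. The plan's own figure**

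Inputs from Sample size calculation: 50% vs 30% readmission, 95% confidence, 80% power, at least 166 patients, 200 recruited. The figure 166 (83 per arm) is reproduced by a one-sided 5% calculation with continuity correction. A two-sided calculation without correction gives 93 per arm, or 186. The present point does not rest on this. The margin for losses is 200 − 166 = 34, and 34/200 = 17%. It covers the number of losses, but no margin corrects a selective loss.

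**3. What selective loss could do (assumed scenarios)**

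The article gives no termination rate. Suppose a share q of the patients who would be readmitted is terminated before the event is recorded, no event-free patient is terminated, and the rest are analysed as observed. With 100 per arm and true rate p:

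- observed rate = p(1 − q)/(1 − pq)
- remaining n = 100(1 − pq)
- power = Φ{[|p₁ − p₂| − 1.96·√(p̄(1 − p̄)(1/n₁ + 1/n₂))] / √(p₁(1 − p₁)/n₁ + p₂(1 − p₂)/n₂)}, two-sided 5%, no continuity correction, with p̄ the pooled rate

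Example, q = 20% control and 10% intervention: control 0.5·0.8/0.9 = 0.444 with n = 90; intervention 0.3·0.9/0.97 = 0.278 with n = 97; difference 0.166.

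| q control / intervention | Observed rates | Difference (points) | Power |
|---|---|---|---|
| 0 / 0 | 50.0% / 30.0% | 20.0 | 0.83 |
| 10% / 10% | 47.4% / 27.8% | 19.5 | 0.80 |
| 20% / 20% | 44.4% / 25.5% | 18.9 | 0.77 |
| 30% / 30% | 41.2% / 23.1% | 18.1 | 0.73 |
| 20% / 10% | 44.4% / 27.8% | 16.6 | 0.66 |
| 30% / 10% | 41.2% / 27.8% | 13.3 | 0.47 |
| 10% / 30% | 47.4% / 23.1% | 24.3 | 0.94 |

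Similar losses in both arms matter little. Unequal losses matter more, and they can bias the difference either way.

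**4. What MAR imputation would repair**

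A simulation of 1,000,000 pairs used an earlier value x and a later value y (assumed correlation 0.6, true mean of y equal to 0). Missing y was filled in by regression on x.

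- Termination when the recorded x exceeds 1: complete-case mean −0.17, after imputation 0.00.
- Termination when the unrecorded y exceeds 1: complete-case mean −0.29, after imputation −0.21.

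Imputation repairs an exit driven by a value that is recorded and in the model. It does not repair an exit driven by something unrecorded. Electroconvulsive therapy and substance use are not among the listed outcomes, so whether they would enter the imputation model is open.

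**The case against.** The strongest case on the other side is that the article promises intention-to-treat three times, imputes what is missing, records reasons for withdrawal for statistical evaluation, expresses relapse events per person-year to allow for variable follow-up, and follows all patients by telephone and record review. On that view only a clarification is missing.

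Part of this stands. Follow-up of terminated patients may in practice continue, and the article does not exclude it. The rest does not settle the matter. The intention-to-treat sentences define who is analysed, not what is collected. A person-year rate handles shorter follow-up only if leaving is unrelated to the event rate. Neither the calls nor the record review are said to yield outcomes to month 12 after termination.

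The objection does defeat several stronger readings that a reader might infer:

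- *That the rule removes relapsing patients.* Relapse and hospitalization are neither termination reasons nor exclusion criteria, and Biostatistical considerations expressly keeps these patients. Any removal would be indirect. A hospitalization before electroconvulsive therapy would already have been counted.
- *That MAR is contradicted.* The imputation model uses the patient's own observed values, and step 4 of the working shows this can suffice.
- *That cholesterol results are cut off at the limits.* The value that triggers an exit is itself measured. Only later values are at risk.
- *That the control arm loses more events and the effect is diluted.* Nothing in the article says so. Closer contact could equally reveal more triggers in the intervention arm.
- *That non-compliance means not taking medication.* The term is undefined.

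**Conclusion.** The point holds as a conflict within the article. Reasons (4) and (5) end study participation, while the intention-to-treat definition and the aim of a complete year presuppose continued observation. Followed as written, the rule can lose primary outcomes selectively.

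The direction and size of any bias cannot be determined from the article. The tabulated differences of 13.3 to 24.3 points are complete-case illustrations with assumed loss shares. They are not forecasts for the planned intention-to-treat analysis with multiple imputation. MAR is made less secure to the extent that termination depends on things not recorded or not modelled. This is a cheap improvement, not a defect that invalidates the design.

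**What to change.** Reconcile Withdrawal or termination from study, Study completion, Data collection, Biostatistical considerations and Missing data:

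1. State that reasons (2), (4) and (5) do not end outcome collection.
2. State that hospitalizations, emergency consultations and unscheduled outpatient visits continue to be taken from the SJDC records to month 12, unless the patient withdraws consent to data use or dies.
3. Use the withdrawal reasons, which are to be recorded anyway, in a sensitivity analysis that departs from MAR for patients whose outcomes are still missing.

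The cost is a short amendment and some extra record review. The clinic records are already a source for the primary outcomes, and the article describes recruitment as still open. The change concerns data collection only. Which clinical stopping rule should apply is not judged here.

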### Study completion

One month before ending the program, patients and their families will be informed about the completion of the study when they have completed 12 months of treatment. For ethical considerations, all patients will be followed periodically by phone calls and further medical history review in the routine control appointment with the physician.

### Randomization

Patients will be assigned to the intervention or the control group through a computer-generated randomization - designed by a person external to the study and otherwise unrelated to it - using Microsoft ® Excel 2007. Participants will be assigned to the treatment groups in sequential order, and the randomization list will be strictly confidential (randomization list maintained off-site by the study coordinator, only one person outside the study knows it). The software generates a sequence of 500 random numbers without repetition (1 to 500), assigning a control group code to 250 numbers and an intervention group code to the other 250. Subsequently, the numbers generated are automatically sorted in ascending order to determine each patient’s allocation to one of the two study groups. Participants will be assigned to the intervention or the control group in sequential order once the study’s coordinator (the pharmacist) verifies fulfillment of inclusion criteria.

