The results could be subject to potential biases because: (1) the patients in this study will not be blinded to treatment assignment, and the same pharmacist, who is responsible for collecting trial data, will observe both the control and the intervention group; and (2) control group patients will receive phone calls from the pharmacist, who will encourage their attendance of appointments. These patients will also receive written material and verbal information about BD, MH, and counseling about the importance of adherence to pharmacological and non-pharmacological interventions to achieve therapeutic goals, as requested by the Human Research Ethical Committee in its approval of this research project. The effect of educational written material and the extra attention received by the patients in the usual care group might produce positive outcomes and reduce the magnitude of the differences with the intervention group.

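### The protocol contradicts itself on who holds the randomization list, and one named holder is the pharmacist who enrols patients, so allocation concealment is not assured

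*Protocol article*

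**What the plan says.** The Randomization section of the protocol article makes these statements:

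- The sequence is computer generated and "designed by a person external to the study and otherwise unrelated to it".
- On secrecy, "the randomization list will be strictly confidential".
- On custody, the bracket that follows reads "randomization list maintained off-site by the study coordinator, only one person outside the study knows it".
- On use, "Participants will be assigned to the treatment groups in sequential order". The list has 500 places, 250 for each group, and no blocks or strata are described.
- On timing, a patient is assigned "once the study’s coordinator (the pharmacist) verifies fulfillment of inclusion criteria".

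Other sections show what the pharmacist does. Under Study population, "the pharmacist will evaluate whether each patient meets all the inclusion criteria and none of the exclusion criteria", and the pharmacist then invites the patient. Patient recruitment and group assignment has the pharmacist informing candidates and seeking their agreement. Intervention design refers to a single pharmacist trained in the Dader Method. The Discussion says that "the same pharmacist, who is responsible for collecting trial data, will observe both the control and the intervention group".

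**The concern.** Allocation concealment means that whoever decides on entry cannot know the next assignment before the decision is final. It is separate from blinding and can be achieved in an open trial, so the statement under Blinding that participants and pharmacists cannot be masked does not settle the matter.

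Here the text names as custodian the person who makes the entry decision, and in the same bracket says that knowledge of the list lies outside the study. Some exclusions leave room for judgement, such as conditions resembling bipolar disorder or an expected inability to follow the protocol. A pharmacist who could see the next place could, even without intending to, apply these criteria differently according to the coming arm. The groups would then differ in prognosis at entry, and intention-to-treat analysis would preserve that difference. The Discussion concedes the open design and the single data collector as possible sources of bias, but is silent on access to the list.

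**Working it through.** **1. The custody statements side by side** (all from Randomization)

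| Statement | Who can know the next assignment |
|---|---|
| The sequence is designed by an external person | That person |
| The list is kept by the study coordinator | The coordinator, unless it is held unseen |
| One person outside the study knows the list | On the ordinary reading, that person alone |
| The coordinator is the pharmacist who verifies eligibility | The coordinator is inside the study |

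On the ordinary reading, rows 2 and 3 conflict once row 4 is added. Two readings would reconcile them:

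- The coordinator stores a sealed copy without being able to read it. Concealment would then hold, but no such seal is stated.
- The coordinator knows the list and just one outsider knows it as well. Concealment would then be absent.

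The text does not choose between these readings.

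**2. Why custody decides the matter**

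Inputs: a list of 500 places, 250 per arm, used in order (Randomization); 200 patients planned (Study population, Sample size calculation). The list is assumed to be in random order.

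The number in one arm among the first 200 is hypergeometric:

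- Mean = 200 × 250/500 = 100.
- SD = √[200 × 0.5 × 0.5 × (500 − 200)/(500 − 1)] = √30.06 = 5.5.
- 95% range = 89 to 111.

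At the edge of that range, the arm with 89 patients has 250 − 89 = 161 of the 300 unused places. The best guess for the next assignment is then right with probability 161/300 = 54%.

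So someone who sees only past assignments can predict very little. Someone who can read the list predicts with certainty. The sequence itself is sound, and concealment depends on who can see it.

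**3. What steering could do (illustration only)**

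Assumptions, none taken from the document: half of candidates are at high risk of readmission (60%) and half at low risk (20%), with no true treatment effect. Then

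spurious difference = (high-risk share in control − high-risk share in intervention) × (0.60 − 0.20).

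| High-risk share, control / intervention | Readmission, control | Readmission, intervention | Difference | Share of the 20-point planned effect (50% v 30%) |
|---|---|---|---|---|
| 55% / 45% | 0.55×0.60 + 0.45×0.20 = 42% | 0.45×0.60 + 0.55×0.20 = 38% | 4 points | 4/20 = 20% |
| 60% / 40% | 0.60×0.60 + 0.40×0.20 = 44% | 0.40×0.60 + 0.60×0.20 = 36% | 8 points | 8/20 = 40% |

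If the gap in risk were 0.20 instead of 0.40, the differences would halve: 0.10 × 0.20 = 2 points and 0.20 × 0.20 = 4 points.

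How much steering is needed? Let x be the fraction of the unwanted risk class still admitted at each place. Then 0.5/(0.5 + 0.5x) is the share of the wanted class.

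- For 0.55, x = 0.82, so about 18% of that class is turned away.
- For 0.60, x = 0.67, so one third is turned away.

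This would have to happen in both arms.

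**The case against.** A reader might infer that allocation in this trial is unconcealed. The document does not support that. The same section describes an external generator, a strictly confidential list, off-site storage and a sole knower outside the study, all of which point to an intention to conceal. A contradictory sentence cannot be treated as proof of one of its halves, and holding a list is not the same as being able to read it. This objection stands, and it limits the point to concealment that is not assured.

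Four further objections deserve an answer.

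- *The order of steps is already right.* Assignment follows verified eligibility and signed consent (Randomization; Patient recruitment and group assignment). That is correct, but it does not help if the person verifying eligibility already knows what comes next.
- *There are checks on screening.* Psychiatrists refer the candidates, and decisions to take part and failures to meet the criteria are registered. These leave an audit trail that can be examined afterwards. They do not conceal the assignment.
- *An article leaves the mechanics of release to the full protocol.* True, and the absence of an envelope or telephone procedure is not the complaint. The complaint is that custody is stated, and stated inconsistently.
- *Adjusted analysis could repair an imbalance.* The multivariable models under Biostatistical considerations include severity, polarity, insight and comorbidity, so they could reduce measured imbalance. They cannot address selection on what was not measured.

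The magnitude illustration is also open to attack. Its risks and steering are all assumed, its overall readmission rate of 40% is below the 50% planned for control, and the 8-point case needs a third of one risk class to be refused. A reader might take 4 to 8 points as an estimate of bias; it is only what is arithmetically possible.

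**Conclusion.** The point holds as an internal contradiction about custody of the list. One of the two stated custodians is inside the study and, as the pharmacist, screens, enrols and collects data in both arms. That this pharmacist also delivers the intervention is an inference from there being one trained pharmacist. Because the list is one fixed sequence used in order, concealment is not assured, and it is absent if the coordinator can read upcoming assignments. Nothing in the document shows that the list was read or that enrolment was steered.

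No size of bias can be derived from the document. The contradiction still needs to be resolved, because the credibility of the whole randomized comparison rests on this step and analysis can make good its loss only in part.

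**What to change.** **For patients still to be randomised** (Trial status says recruitment continues): state that the external person who generated the list is its only holder. That person releases one assignment at a time, and only after the pharmacist has recorded eligibility and consent, an order the protocol already requires. Name the means of release, for example a telephone call or message from that person, or sequentially numbered opaque sealed envelopes prepared by that person.

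**For patients already randomised:** the first was randomised on 24 November 2011, 18 months of recruitment were planned, and the article appeared in May 2014, so most assignments had probably been made. For them the remedy is disclosure. Report who actually held the list and whether the enrolling pharmacist could see upcoming assignments, and compare baseline risk by arm. The custody phrase should not simply be deleted. If it is true, it must be reported.

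**Cost:** a corrected sentence, a small release step by a person already in the plan, and a short account in the trial report. There is no change to sample size, visits or treatment. The baseline comparison can reveal measured imbalance but cannot prove that selection did not occur.
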